## Discussion and Dissemination

This study protocol aims to investigate the neuromodulatory effects of tDCS in patients with a history of MTBI who developed PPCS with a current subjective complaint involving long-term episodic memory, working memory, and executive function. Additionally, the study aims to verify the hypothesis that tDCS exerts pro-cognitive effects in the described population.

Interesting findings have emerged from both clinical trials and neuropsychological studies using tDCS. Knowledge about the cognitive and behavioral functions of brain lesions together with sophisticated neuroimaging techniques have provided major contributions to the fields of neuropsychology and cognitive neuroscience.

The interest in this topic arises from the understanding that neuromodulation techniques can provide causal data that answer questions about the effect of stimulation on cortical structures and specific cognitive functions. The modulatory effect of neuromodulatory stimulation on executive function is of particular interest for understanding the mechanisms underlying the integration of cognition with behavior.

The data that will be obtained in this study may help to provide a step forward for neuropsychology and cognitive neuroscience, as the results will help to reveal brain functioning and the effects derived from interventions. This study also may produce new information regarding the possible pro-cognitive effects of tDCS. Therefore, therapeutic interventions in subsequent studies may be investigated, since the present study will use only a single session of tDCS. We decided to initially study the immediate effects of tDCS in such patients because of the following reasons: (1) we will study a specific population of TBI patients, then, as the first study to evaluate the referred outcomes, we believe that we need to have preliminary data to move forward. (2) We do not know what is the best region to be stimulated, and this trial probably will be able to solve this issue.

This study is expected to initiate a discussion about PPCS thus contributing to the creation of public health policies to treat this underdiagnosed disease. On one hand, PPCS affects a patient’s life in social, work, and cognitive contexts. On the other hand, these patients are poorly supported, and their condition is rarely established based on the findings of imaging exams; this lack of evidence could lead to difficulty in diagnosing and treating PPCS patients.

We believe that tDCS holds great promise. It has been shown in previous studies that tDCS is successful, capable, inexpensive, and safe for use in the treatment of a wide range of neurological conditions. Thus, the application of tDCS might improve the efficiency of different neurorehabilitation techniques and provide further relief to patients suffering from long-term disabilities.

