### Randomization and Blinding

Randomization will be done *via* a computer-produced randomized controlled table. All the 20 patients will be randomized into the three types of stimulation: frontal stimulation, temporal stimulation, and sham stimulation. The neuropsychologists and the patients will be blinded for the type of stimulation performed in each session.

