### Sample Size Calculation

Most studies which aimed to assess the effects of non-invasive neurostimulation on cognitive function in TBI were case reports or small open labels studies. Moreover, there have been no previous studies comparing the cognitive effects of tDCS stimulation in patients with PPCS. Considering that there were no prior data on the effects of A-tDCS on patients with PPCS using our primary outcome measure, a formal sample size calculation was not possible; thus, we estimated that enrolling 30 patients would be a reasonable approach for an exploratory trial.

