### Statistical Analysis

All analysis will be performed using Statistical Package for Social Sciences software version 23.0 for Windows (Prentice Hall, Chicago, IL, USA). A significance level of *p* < 0.05 will be considered for all tests. The quantitative variables will be described using the mean and SDs for normally distributed data or median with inter-quartile range for non-parametric data. The qualitative variables will be presented as absolute and relative frequencies. The five neuropsychological assessments will be summed and averaged to create a composite score. Cohen’s *d* will be calculated to compare the changes in the neuropsychological scores between the groups. An analysis of variance will be used to test whether there is an overall effect of any type of active stimulation on each outcome measure. When appropriate, we will perform *post hoc* paired comparisons using Bonferroni correction for multiple comparisons.

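### The site comparison is part of the primary hypothesis and is expected to settle the best region, but the plan reaches it only as a conditional post hoc test, with no precision stated

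*Protocol article*

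**What the plan says.** All statements are in the protocol article.

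- **Primary Outcome Measures:** the primary hypothesis is that L-DLPFC stimulation does better than each of the other two conditions, sham and L-TC. The site contrast is therefore half of the primary hypothesis.
- **Discussion and Dissemination**, among the reasons for starting with immediate effects: "We do not know what is the best region to be stimulated, and this trial probably will be able to solve this issue". The reason given just before it is that preliminary data are needed.
- **Statistical Analysis:** "An analysis of variance will be used to test whether there is an overall effect of any type of active stimulation", separately for each outcome. Pairwise comparisons follow post hoc with Bonferroni correction, and only where considered appropriate. Cohen's d is to be calculated for changes between conditions, with no condition attached. The significance rule is: "A significance level of *p* < 0.05 will be considered for all tests".
- **Sample Size Calculation:** "there were no prior data on the effects of A-tDCS on patients with PPCS using our primary outcome measure", so "a formal sample size calculation was not possible", and "we estimated that enrolling 30 patients would be a reasonable approach for an exploratory trial".
- **Abstract and Procedure:** two active sites plus sham, with every patient receiving all three.
- **Randomization and Blinding:** "All the 20 patients will be randomized into the three types of stimulation". The Abstract, Participants and Sample Size Calculation sections all give 30.

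**The concern.** The hypothesis, the stated expectation and the analysis do not line up. The hypothesis names two contrasts, and the Discussion expects one of them to be resolved. The analysis is aimed at a different question, whether the conditions differ at all, and makes the named contrasts follow-up tests whose use is left open. If the overall test is not significant, the text commits to no test of L-DLPFC against L-TC.

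The expectation also goes beyond the design. Two tested sites can be ranked against each other, but that does not identify the best region to stimulate. Nothing in the article shows how precise even that ranking would be.

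Site choice is a stated reason for the trial, and later therapeutic studies are meant to build on it. Without a named estimate and interval, a non-significant site contrast could be read as evidence that the sites are equal, or a chance ordering as evidence that the question is solved.

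**Working it through.** **Nothing to reproduce.** The article states no power, effect size, SD or within-patient correlation. The figure of 30 is a judgement.

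**Inputs from the article.** n = 30, or 20 under Randomization and Blinding. It is a crossover, so each contrast has n pairs. Three conditions give three pairs. The significance level is 0.05.

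**Assumptions.** Two-sided tests (sidedness is not stated), no dropout (which favours the trial), Bonferroni over the three pairs (0.05/3 = 0.0167), one outcome at a time, and a simple paired t-test. The effect d is the true L-DLPFC minus L-TC difference divided by the SD of the within-patient difference. The values of d are assumed.

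**Formula.** Noncentral t with df = n − 1 and noncentrality d√n. For d = 0.3 and n = 30 the noncentrality is 0.3 × 5.477 = 1.643. At 0.05/3 this gives power 20.3%. The normal approximation, Φ(1.643 − 2.394), gives 22.6%.

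**Power of the Bonferroni site contrast (0.05/3):**

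| Site difference (SD of paired difference) | n = 30 | n = 20 |
|---|---|---|
| 0.2 | 8.9% | 5.9% |
| 0.3 | 20.3% | 12.5% |
| 0.4 | 37.8% | 23.0% |
| 0.5 | 58.3% | 37.3% |
| 0.6 | 76.7% | 53.5% |
| 0.8 | 96.1% | 81.8% |

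- Power of 50% needs a difference of 0.46 SD (n = 30) or 0.58 SD (n = 20).
- Power of 80% needs 0.62 SD or 0.78 SD.

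**A single direct contrast at 0.05.** At 0.3 SD, power is 35.5% (n = 30) or 24.7% (n = 20). At 0.5 SD it is 75.4% or 56.5%.

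**Effect of an ANOVA gate.** Suppose the pairwise test is run only after a significant overall ANOVA. In simulation (20,000 runs per scenario, equal variances, correlation 0.5, 0.3 SD site gap, three patterns of means) the Bonferroni contrast succeeded in 19.5 to 19.8% of runs at n = 30 and 11.4 to 12.1% at n = 20. Against 20.3% and 12.5% ungated, the gate costs about one percentage point.

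**Sensitivity to the unit.** If 0.3 is in SDs of the score, then d = 0.3/√(2(1 − ρ)), where ρ is the between-session correlation. Bonferroni power is:

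| ρ | n = 30 | n = 20 |
|---|---|---|
| 0 | 9.9% | 6.5% |
| 0.5 | 20.3% | 12.5% |
| 0.8 | 53.0% | 33.3% |
| 0.9 | 86.3% | 64.7% |

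**Precision, which needs no assumed effect.** The 95% half-width in SDs of the paired difference is t(0.975, n − 1)/√n:

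- n = 30: 2.045/5.477 = 0.37.
- n = 20: 2.093/4.472 = 0.47.

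**The case against.** The Discussion sentence is hedged, the trial is called exploratory, the need for preliminary data is acknowledged, and the article is open about testing only two regions. No decision rule depends on the sentence. That is fair, and it keeps this a matter of wording and prespecification. It does not remove the mismatch between the primary hypothesis and the stated analysis route, because the article fixes both.

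Four stronger readings are tempting, and the documents do not support them.

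- *The trial has about 20% power for the site question.* That figure belongs to one assumed difference, 0.3 SD, in one unit. At n = 30, Bonferroni power runs from 9% to 96% over the values shown.
- *A non-significant site result is the likely outcome for a moderate difference.* If moderate means 0.5 SD, a significant result is the likelier one at n = 30 (58% with Bonferroni, 75% at 0.05). The statement holds only for smaller differences or, with Bonferroni, for n = 20.
- *The site comparison may not be reported at all.* Cohen's d between conditions is planned without condition. What is missing is a named contrast and an interval.
- *The site contrast is the weakest part of the analysis.* All three pairs share the same n and the same threshold. One is weaker only if its true effect is smaller or its paired differences vary more, and the article says neither. A strict ANOVA gate is itself only one reading of the conditional wording, and it costs about one percentage point.

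It can also be said that 30 against 20 patients is a separate error. It is, but it must be settled before any statement of precision can be made.

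**Conclusion.** The point stands as a mismatch that is cheap to correct. A contrast named in the primary hypothesis, and expected in the Discussion to be resolved, is tested only conditionally and post hoc, and the planned effect size has neither a named contrast nor an interval. The design can rank two sites but cannot identify the best region, and the Sample Size Calculation section gives no support for expecting even the ranking to be settled.

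That much rests on the article's text alone. The power figures rest on assumed effects, two-sided paired tests, Bonferroni over three pairs and no dropout. They show that whether the site question is more likely than not to be answered depends on a true difference of at least about 0.46 SD of the paired difference at n = 30, or 0.58 SD at n = 20. The article gives no reason to expect a difference above or below those values.

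**What to change.** 1. **Statistical Analysis:** prespecify the two primary-hypothesis contrasts, L-DLPFC minus sham and L-DLPFC minus L-TC, as direct within-patient estimates with 95% confidence intervals, reported whatever the ANOVA shows. The ANOVA, the Bonferroni comparisons and Cohen's d can stay.
2. **Discussion and Dissemination:** replace the claim about resolving the best region with wording such as: *The trial will estimate the difference between the two tested sites, with an expected 95% confidence interval half-width of about 0.37 SD of the paired difference with 30 patients. A non-significant difference will not be read as showing that the sites are equal.* If the number is 20, the half-width is 0.47 SD.
3. **Randomization and Blinding:** reconcile 20 patients with the 30 given elsewhere.

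The cost is slightly more reporting and a less favourable stated promise. No extra patients or assessments are needed.

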## Ethics Statement

Ethics approval has been obtained from the Ethics Committee for Analysis of Research Projects, Hospital das Clínicas, University of São Paulo (CAPPesq 612.643/14). Written informed consent will be obtained from all participants.
